## Introduction

### Background

 Pulmonary embolism (PE) is a potentially fatal condition that may cause right ventricular failure and death if not recognised and treated promptly. In the UK, PE accounts for almost 70 000 hospital presentations and 37 000 hospital admissions per year.^1^ This places a substantial financial and operational burden on the NHS. Although it is difficult to know precise cost estimates, the total cost burden for venous thromboembolism is estimated at £640 million per year.^2^ Furthermore, the incidence of PE is rising.^3^,^5^ This trend can be partially explained by the increasing availability and improved quality of diagnostic imaging. However, demographic and clinical factors, such as increased survival among patients with major prothrombotic comorbidities and obesity, are also likely to contribute to this increase.^6^

Although falling, mortality from PE remains significant. It accounts for up to 6.5 deaths per 100 000 population per year.^6^ The reduction in mortality is attributed to improved interventions, including direct oral anticoagulants, better management guidelines^7^ and increased diagnosis of smaller, subsegmental emboli.^8^ However, despite advances in PE detection and clear national guidance on acute PE treatment, risk stratification and management are still performed poorly.^9^

Radiological imaging plays a critical role in the PE pathway. Multi-detector CT pulmonary angiography (CTPA) is considered the gold standard imaging modality for PE diagnosis. CTPA can also provide important, prognostically relevant information on right heart strain (RHS).^10 11^ This includes reversal of the right ventricular to left ventricular ratio (RV:LV), interventricular septal straightening and contrast reflux in the inferior vena cava. These indirect markers can inform risk stratification and subsequent clinical medical management.

The NHS Long Term Plan outlines the importance of innovative, affordable technologies to improve diagnosis, risk assessment and treatment of respiratory conditions, including PE.^12^ Achieving this depends on accurate image interpretation and timely communication of findings. However, national audits, including the National Confidential Enquiry into Patient Outcome and Death, have highlighted deficiencies in PE reporting and downstream clinical.^9^

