##### Unequivocal PE

The research team will only intervene if the AI software identifies an unequivocal acute PE that appears to have been missed or not reported in the intervention cohort. These cases will be escalated to a thoracic radiologist for urgent review to ensure appropriate treatment. A study-specific standard operating procedure has been designed to manage this process while maintaining patient safety.

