### Statistical analysis

#### Clinical and radiological outcomes

Our primary outcome will be the proportion of patient decisions made in line with evidence-based best practice guidelines after introducing AI technology within CTPA reporting. Secondary outcomes relate to acute PE detection, RV:LV ratio quantification and clinical and operational endpoints including mortality, length of stay, readmission, follow-up and cost to NHS (table 1).

**Table 1 T1:** Primary, secondary and additional outcomes

Outcome measure	Measure description
Primary outcome measure	
Proportion of patient decisions made in line with evidence-based best practice guidelines after introducing AI technology within CTPA reporting	Comparison before and after AI introduction
Secondary outcome measures	
Rate of acute PE detection with AI technology	True positives and true negatives
Rate of discordant acute PE cases	False positive and false negative rate with acute PE detection
AI failure rate for acute PE detection	Proportion of scans unable to be interpreted by AI despite suitable CTPA acquisition
Rate of RV:LV detection with AI technology	True positive and true negative
Rate of discordant RV:LV detection	False positive and false negative
Failure rate for automated RV:LV ratio	Proportion of scans unable to calculate automated RV:LV ratio despite suitable CTPA acquisition
30-day mortality	Patient mortality (death) at 30-days post-PE diagnosis. Comparison before and after AI introduction
12-month mortality	Patient mortality (death) at 12 months post-PE diagnosis. Comparison before and after AI introduction
Hospital admission and bed days for acute PE	Comparison before and after AI introduction
Time to anticoagulation in PE cases	Comparison before and after AI introduction
Time from CTPA to discharge	Comparison before and after AI introduction
PE risk stratification rates (low, intermediate low, intermediate high and high risk)	Comparison before and after AI introduction
Cost to NHS for acute PE	Comparison before and after AI introduction
End-user (clinician and radiologist) acceptability of AI technology	Quantified metrics from a non-validated questionnaire to evaluate end-use experience of integrated AI radiology reporting
Referral rates to outpatient follow-up (respiratory, thrombosis, haematology)	Comparison before and after AI introduction
Diagnostic rate of chronic thromboembolic pulmonary hypertension	Comparison before and after AI introduction
Additional outcome measures	

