#### Artificial intelligence accuracy

We will evaluate AI performance against both the original radiology reports and expert thoracic radiologist reviews, which will serve as the clinical reference standard. Agreement between modalities will be assessed using Cohen’s kappa and measures of diagnostic test performance.

The research team will also review all PE-positive and discrepant cases to evaluate the potential for the AI software to act as a clinical safety net for the detection of acute PE.

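### Mortality, time to anticoagulation and risk class are compared among diagnosed PE cases, a group whose membership the AI can change in the intervention cohort only

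*Protocol article*

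**What the plan says.** Table 1 (Clinical and radiological outcomes) words the two mortality outcomes as "Patient mortality (death) at 30-days post-PE diagnosis" and "Patient mortality (death) at 12 months post-PE diagnosis. Comparison before and after AI introduction". It lists "Time to anticoagulation in PE cases" and the rates of the four PE risk classes, also compared before and after AI.

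Under CT report interpretation, each scan is classed as PE-positive or PE-negative from its radiology report. In the comparator cohort the AI is run afterwards and cannot affect that report. In the intervention cohort it alerts the reporting radiologist to suspected PE. The section on unequivocal PE adds a step in the intervention cohort alone: "The research team will only intervene if the AI software identifies an unequivocal acute PE that appears to have been missed" or left unreported.

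Statistical analysis specifies t-tests and χ² tests, then regression with a step at AI implementation. Adjustment for Geneva and sPESI predictors is made only if feasible. Participant data says that outcomes to 12 months, including all-cause mortality, are collected for each participant.

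**The concern.** The denominator of these outcomes is fixed after the intervention and partly by it. A PE seen only because the AI flagged it counts as a case in the intervention cohort; the same PE, unflagged and unreported in the comparator cohort, counts as negative. The two PE groups are then not alike, and outcome rates can move although every patient fares the same. This is stage migration.

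The protocol supplies reasons to expect it. The Background attributes part of the fall in PE mortality to "increased diagnosis of smaller, subsegmental emboli", and the section on AI in radiology reports that algorithms have detected PE better than radiologists. At stake is whether a lower PE mortality, or a larger low-risk share, after AI can be read as a clinical effect. The Clinical management section expects outcome differences to reflect how radiologists and clinicians use the AI findings, and makes no allowance for a change in who is counted.

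**Working it through.** The protocol gives no power calculation or expected event rate, so there is no figure of its own to reproduce.

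**Inputs from the protocol.** About 3500 eligible CTPAs over 24 months; PE prevalence 12 to 15% (Sample size). Significance at p < 0.05 (Statistical analysis).

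**Assumptions, not in the protocol.** An equal split between cohorts; one scan per patient; two-sided testing; baseline 30-day PE mortality m; extra PE cases found with AI as a fraction x of the cases found without it; mortality e in those extras; baseline low-risk share L.

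**PE cases per cohort.** 3500/2 = 1750. 1750 × 0.12 = 210; 1750 × 0.15 = 262.5, about 263.

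**Mortality with no patient benefiting.** Rate after = (m + x·e)/(1 + x).
- m = 6%, x = 10%, e = 0: 0.060/1.10 = 5.5%
- m = 6%, x = 10%, e = 1%: 0.061/1.10 = 5.5%
- m = 6%, x = 20%, e = 0: 0.060/1.20 = 5.0%
- m = 6%, x = 20%, e = 1%: 0.062/1.20 = 5.2%

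With 210 to 263 baseline cases, a normal approximation gives about a 4 to 8% chance that this shift alone yields p < 0.05 in favour of AI, against 2.5% with no shift. Over a wider grid (m = 5 to 12%, x = 5 to 25%, e = 0 to 2%) the spurious risk ratio runs from 0.97 to 0.80 and that chance from about 3 to 16%.

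**Risk class, every extra case low risk.** Share after = (L + x)/(1 + x), with L = 40%.
- x = 10%: 0.50/1.10 = 45%
- x = 20%: 0.60/1.20 = 50%
- x = 25%: 0.65/1.25 = 52%

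With 236 baseline cases (1750 × 0.135), the chance of p < 0.05 from the shift alone is about 23% at x = 10% and 79% at x = 25%.

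**Opposite case: AI removes false-positive reports.** If a fraction f of baseline cases with 2% mortality is dropped, rate after = (m − f × 0.02)/(1 − f). For m = 6%: f = 5% gives 0.059/0.95 = 6.2%; f = 10% gives 0.058/0.90 = 6.4%. PE-only mortality rises, again with no change in any patient's outcome.

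**All scanned patients as denominator.** Relabelling a scan changes neither the deaths nor the 1750 patients, so the spurious difference is zero in every scenario above.

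**Do the planned analyses remove the shift?** The simple tests do not adjust. The regression step falls at AI implementation, the moment ascertainment changes, so it absorbs the shift into the AI effect. Geneva and sPESI adjustment is conditional and cannot identify which cases would have been missed without AI. The expert reference standard covers four months of the comparator cohort, so it gives no AI-independent PE definition across both.

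**The case against.** The strongest reply is that these are secondary outcomes of a self-described exploratory feasibility study, that direction and size rest on assumed inputs, and that sensitivity analyses may sit in an analysis plan not shown. Much of this stands. The mortality shift is small, and the direction is not settled by the documents. But the diagnosis-based outcome definitions are fixed in the protocol itself, and a later plan would inherit them.

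A reader might infer four stronger things that the text does not support.
- That the bias must flatter the AI. Removal of false positives would reverse it.
- That the primary outcome is biased in the same way. It concerns the proportion of patient decisions in line with guidelines, with no stated PE-only denominator, so any effect on it is conditional.
- That escalated cases certainly enlarge the PE group. The protocol does not say they join it, and since escalation covers only unequivocal PE, they need not be small emboli.
- That bed days are diluted too. "Hospital admission and bed days for acute PE" could mean cohort totals, which extra cases would raise.

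Nor does the protocol say that PE-only comparisons are the sole ones intended; it simply states no all-CTPA version of these outcomes.

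**Conclusion.** The concern holds for 30-day and 12-month mortality, time to anticoagulation and risk class. Each is compared in a group that the AI can alter in one cohort only, and no stated analysis corrects for it. Enlargement by lower-risk cases is the likely direction, not a certain one; in either direction the PE-only contrast mixes ascertainment with care.

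Under the stated assumptions the mortality artefact is about 0.5 to 1.0 percentage points on 6.0% and would seldom reach significance alone. Risk class is the more exposed outcome, at about 5 points on 40% with 10% extra cases, if all of them are low risk. For time to anticoagulation the direction is open and no size is estimated.

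**What to change.** 1. Add 30-day and 12-month all-cause mortality in all eligible CTPA patients, timed from CTPA, as the comparison that supports any mortality claim. Keep the PE-only results as secondary, labelled as open to a change in ascertainment.
2. Report the PE-positive rate per CTPA in each cohort, and give risk-class counts per CTPA scanned as well as per PE case.
3. Flag PEs found only through research-team escalation and repeat the PE-only analyses without them.

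A common PE definition that adds AI-positive, report-negative cases should be an optional sensitivity analysis at most. The protocol plans that "The research team will also review all PE-positive and discrepant cases", but the review is not stated to be blinded or done by experts, and it would have to cover both cohorts. It should not be used for time to anticoagulation, because a comparator PE that nobody reported may have no treatment time.

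**Cost.** The mortality data are already to be collected for every participant, so items 1 to 3 need wording, a flag and extra tables. The price is precision: about 85 to 88% of scanned patients have no PE (100% minus 15 or 12%), so a true 1-point fall in mortality among PE patients appears as 0.12 to 0.15 points among all scanned (1 × 0.12 to 1 × 0.15).

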### Study population and setting

Study participants will be recruited from consecutive, clinically indicated CTPAs performed for the assessment of acute PE at Royal United Hospitals Bath NHS Foundation Trust in England. Scans from both inpatient and outpatient settings will be included. Ethical approval for participant inclusion has been granted by West of Scotland Research Ethics Service (23/WS/0067, 3 May 2023).

The pre-implementation (comparator) cohort will be retrospectively identified over a 12-month period preceding AI deployment. Following a 1 month implementation phase, the post-implementation (intervention) cohort will be prospectively recruited over the subsequent 12 months. Prospective recruitment will complete on 7th January 2025.

All participants will meet the following eligibility criteria:

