### Sample size

As a pragmatic real-world quasi-experimental assessment of AI integration, formal power calculations were not feasible. Based on historic imaging volumes, it is anticipated that approximately 3500 eligible CTPAs will be identified across the 24-month recruitment period and that the prevalence of acute PE will be between 12% and 15%.

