##### Intervention cohort: AI technology plus usual care

AI tools will be integrated prospectively into radiology workflows within the intervention cohort. The AI technology features a priority flagging system which alerts radiologists to suspected PE cases. This prioritisation process does not re-order the RIS queue or auto-populate any radiology report. Instead, the AI software generates key-slice images and RV:LV ratio overlays that are directly accessible within the PACS and AIDOC Desktop App. This allows the reporting radiologist to consider the AI output at their discretion when reporting. Verification of the final radiology report will remain the responsibility of the reporting radiologist.

For CTPAs not analysed by the AI technology due to technical issues, standard reporting procedures will be followed.

During the intervention phase, radiologists will have the option to provide direct feedback on AI outputs via the priority flagging system, including free-text commentary if desired. All cases in which there is a discrepancy between the AI output and radiology report will be reviewed by the research team as part of a predefined sub-analysis. This will allow assessment of radiologist engagement with the AI outputs, its diagnostic accuracy and clinical relevance in routine practice.

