## Methods: data collection, management and analysis

### Data collection and management

For each eligible participant, a structured CRF will be completed to capture relevant data. Only the minimum necessary data required to address the study objectives will be collected. Participants will be assigned a unique study identification code to pseudonymise their data. A cross-referencing list linking identifiers to study codes will be stored securely on a password-protected NHS computer database. All research records will be retained for 5 years, after which they will be securely destroyed.^22^

For the comparator cohort, anonymised CTPA images will be transferred for off-site analysis at AIDOC’s core laboratory (Tel-Aviv, Israel). Prior to image transfer, all imaging will be anonymised in accordance with the Royal United Hospitals Bath NHS Foundation Trust’s information governance protocols to ensure data confidentiality.

In the intervention cohort, AI solutions will be embedded within existing PACS workflows. AIDOC and IMBIO servers will be installed locally, facilitating real-time ‘live’ AI analysis of CTPAs. System integration will be conducted in collaboration with radiology information technology and information governance teams.

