#### Health economics

An exploratory decision analysis model will be developed. The model will assess the cost-effectiveness of integrating AI technology within the diagnostic workflow for acute PE. The model includes a decision tree component and Markov cohort. The decision tree will model the diagnosis, treatment and clinical outcomes for acute PE. Evidence for the decision tree will be derived from the comparator cohort. The Markov cohort will evaluate the lifetime costs and outcomes for acute PE. Evidence for these costs will be drawn from the literature on the consequences of the post-pulmonary syndrome. Unit costs associated with radiological imaging, hospitalisation and treatment will be extracted from NHS reference costs, unit costs of health and social care and the hospital finance team.

Uncertainty in parameter inputs will be accounted for in the analysis by including parametric distributions at each point estimate. In cases where the evidence is not sufficiently detailed, expert opinion will be used to estimate the most plausible distribution. Threshold analysis will be used to address the commercially sensitive nature of the cost of adopting the AI technology. Results from the model will be reported as incremental cost-effectiveness ratios and expected net monetary benefit. Cost-effectiveness acceptability curves will show the impact of uncertainty in the cost-effectiveness.

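### The before/after cost outcome covers acute PE only, although the stated economic aim covers everyone scanned for suspected PE

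*Protocol article*

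**What the plan says.** In the protocol article, Table 1 (Clinical and radiological outcomes) lists "Cost to NHS for acute PE" as a secondary outcome, described only as a comparison before and after AI introduction. It is the only before/after cost outcome in the table.

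The Study aim and the strengths and limitations box both place the economic question in people with suspected PE. Study population and setting recruits from "consecutive, clinically indicated CTPAs performed for the assessment of acute PE", so confirmed PE is not required for entry. In the intervention cohort the servers are installed locally, "facilitating real-time ‘live’ AI analysis of CTPAs" (Data collection and management). The stated exception is: "For CTPAs not analysed by the AI technology due to technical issues, standard reporting procedures will be followed".

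Sample size expects that "approximately 3500 eligible CTPAs will be identified across the 24-month recruitment period". The same section puts the expected share of scans with acute PE at 12% to 15%.

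Health economics describes a separate exploratory model: "The decision tree will model the diagnosis, treatment and clinical outcomes for acute PE". Evidence for the tree comes from the comparator cohort. On price, the section says: "Threshold analysis will be used to address the commercially sensitive nature of the cost of adopting the AI technology".

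**The concern.** The technology acts on everyone scanned, but the cost comparison is worded for the minority who turn out to have PE. The wording looks deliberate. In the same table, the rows on bed days and on time to anticoagulation are also limited to PE, while the row on time from scan to discharge is not. Such a qualifier therefore reads as a restriction on who is counted.

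Two things are at stake. First, some plausible cost effects of AI arise in patients without PE: extra work after a false alarm, and a shorter or longer stay after a negative scan. Table 1 counts false positives and measures time to discharge, but ties no cost to either. Second, the PE group is defined by a diagnosis that AI may alter. The study asks whether AI improves diagnostic accuracy, and the Unequivocal PE section provides for escalation of apparently missed PEs in the intervention cohort only. The two PE groups may then differ in case mix because of the intervention itself, and a lower cost per PE patient could coexist with a higher total cost.

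**Working it through.** The plan states no cost, power or break-even figure, so there is nothing to reproduce. The check compares populations and uses simple arithmetic.

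**Inputs.** From Sample size: N = 3,500 eligible CTPAs over 24 months, and prevalence p = 0.12 to 0.15. Assumption: an even split, so 3,500 / 2 = 1,750 per cohort. The protocol gives no rate of scans left unanalysed by AI and no specificity to plan on, so both are varied below as assumptions.

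**1. Share and number outside the cost outcome.** Share without PE = 1 − p.
- p = 0.12: 1 − 0.12 = 88%. PE cases 3,500 × 0.12 = 420 (210 per cohort); without PE 3,500 − 420 = 3,080 (1,540 per cohort).
- p = 0.15: 1 − 0.15 = 85%. PE cases 3,500 × 0.15 = 525 (262.5 per cohort); without PE 3,500 − 525 = 2,975 (1,487.5 per cohort).

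**2. False alarms among them.** Number per cohort = (1 − specificity) × 1,750 × (1 − p), taking every scan as analysed.

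| Assumed specificity | p = 0.12 | p = 0.15 |
|---|---|---|
| 100% | 0 | 0 |
| 97% | 46 | 45 |
| 95% | 77 | 74 |
| 90% | 154 | 149 |

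The number may be trivial or may approach the number of PE cases in a cohort. The protocol does not allow it to be fixed in advance.

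**3. Effect of a PE group that changes with AI.** Illustration with assumed figures: 210 PE patients cost 1 unit each before AI, and afterwards 20 milder cases are added at 0.5 unit each.
- Total before: 210 × 1 = 210. Total after: 210 + 20 × 0.5 = 220.
- Mean per PE patient: 1 before, 220 / 230 = 0.957 after, a fall of 4.3%.
- Total PE cost: 220 / 210 = 1.048, a rise of 4.8%.

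The mean falls although no patient has become cheaper to treat. A mean over all eligible CTPAs does not condition on the diagnosis and so does not have this problem.

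**4. Conversion between units for a price threshold.** Scans per PE = 1 / p: 1 / 0.15 = 6.7 and 1 / 0.12 = 8.3. If 5% to 10% of scans are not analysed (assumed), analysed scans per PE = (1 − f) / p: 7.9 to 7.5 at p = 0.12, and 6.3 to 6.0 at p = 0.15. This is only the reciprocal of prevalence. It shows how far a per-PE price and a per-scan price differ, and it measures no error in the plan.

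**The case against.** A reader might go further and infer that AI running cost is left out altogether, that the economic model ignores negative scans, and that the affordable price will be overstated 6.7 to 8.3 times. The document supports none of these.

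- **AI cost.** Health economics deals with the cost of adoption by threshold analysis, so it is in the plan.
- **The model.** The tree includes diagnosis, the model is set in the diagnostic workflow, and its evidence comes from the comparator cohort, which is all eligible CTPAs. It may well start at suspected PE already; the text neither confirms nor excludes this. The article also uses the phrase about acute PE loosely elsewhere, for example for AI access that covers everyone scanned.
- **The price factor.** No per-PE threshold is stated. Tree entry point and threshold unit are details that a condensed article may leave to the full plan.

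It can also be argued that a PE-specific cost outcome beside a separate decision model is a sensible division of work. A cost over all scanned patients, inpatients included, brings in stays caused by other illness and could hide an effect on PE care. That is a real drawback, and a good reason to keep the PE figure. It does not make the PE figure an answer to the question in the Study aim, and the model is labelled exploratory. False positives and time to discharge are indeed measured, so the gap lies in costing them and not in collecting them.

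**Conclusion.** The point holds for the Table 1 cost outcome alone. Its population is narrower than the aim it serves: 85% to 88% of scanned patients, about 1,490 to 1,540 per cohort, are outside it, and the remainder are selected on a diagnosis that AI can change. These counts rest on the protocol's own prevalence and volume and on an even split between cohorts. The direction and size of any resulting bias in cost cannot be given, because the protocol states no costs, no specificity to plan on and no expected change in detection; the 4.3% fall against a 4.8% rise is an illustration only. The conclusion also rests on reading the qualifier in the row as a restriction, which the neighbouring rows support. It does not extend to the AI price or to the decision model. Cost is a secondary outcome, but it is the observed figure closest to an adoption decision, so the change is worth making.

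**What to change.** Add to Table 1 the mean NHS cost per patient with an eligible CTPA, compared before and after AI introduction, and name it as the cost outcome that answers the Study aim. Keep the cost for acute PE patients alongside it as a descriptive figure, and state how PE status is assigned for it.

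The AI price can stay in the threshold analysis. Reporting that threshold per scan would avoid a misreading; this is a courtesy to the reader and corrects no error.

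Cost: about 2,975 to 3,080 more patients to cost across the two cohorts. Participant data already lists admission and discharge times among the items collected for each participant, and Health economics already names the sources of unit costs, so no further recruitment is needed. The added outcome will carry more variation from illness unrelated to PE, so its estimate may be less precise and an effect confined to PE care harder to see. Showing the two figures together meets that drawback.

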### Study design

This pragmatic, single-centre, non-randomised, quasi-experimental cohort study will evaluate clinical and radiological outcomes in two distinct patient cohorts. The comparator cohort is defined as *usual care*; general radiologist reporting of CTPA. This cohort will consist of patients recruited retrospectively, prior to implementation of the AI. The intervention cohort is defined as *integrated AI technology AND usual care*; general radiologist reporting of CTPA with access to AI technology for acute PE detection. This cohort will consist of patients recruited prospectively, following the implementation of the AI.

The study will consist of three distinct phases. The pre-implementation and post-implementation phases will derive the comparator and intervention cohorts, respectively. The implementation phase will ensure installation, testing and appropriate training of the AI technology. Figure 1 outlines the study structure.

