Exploratory outcomes	Given the exploratory nature of this observational non-randomised feasibility study, there may be patterns/outcomes which emerge/develop during the study period. The investigators will report on any patterns that may emerge following the introduction of AI reporting

AI, artificial intelligence; CTPA, CT pulmonary angiography; PE, pulmonary embolism; RV:LV, right ventricular to left ventricular ratio.

Descriptive statistics will summarise participant baseline characteristics and comorbidities, separately in the comparator and intervention cohorts. Our primary analyses will consist of comparisons between the comparator and intervention cohorts, with continuous outcomes analysed using t-tests and categorical outcomes using χ^2^ tests. To account for and disentangle any possible underlying time trends from the effects of AI introduction, regression models will be used to compare outcomes. These will include covariates that allow for a linear trend in the pre-implementation phase, a step change at the point of AI implementation, and a modification to the linear trend following this.

Kaplan-Meier survival curves will quantify differences between time-to-event outcomes in the two cohorts. Cox regression models will also be used to summarise the difference between cohorts. If feasible, regression models will be adjusted for known predictors of outcome from both Geneva and sPESI scoring systems.^20 21^ Missing values will be handled by performing each analysis excluding patients who have relevant data missing for the variables concerned. Statistical significance will be set according to p value <0.05.

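### The primary analysis of this non-randomised before/after study is an unadjusted chi-squared test, although the protocol itself says regression is needed to separate time trends from the AI effect

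*Protocol article*

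**What the plan says.** The Study design section describes the study this way: "This pragmatic, single-centre, non-randomised, quasi-experimental cohort study will evaluate clinical and radiological outcomes in two distinct patient cohorts". Under Clinical and radiological outcomes, the endpoint is a proportion: "Our primary outcome will be the proportion of patient decisions made in line with evidence-based best practice guidelines".

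The same section then sets out the analysis in four steps.

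- **Primary analysis.** "Our primary analyses will consist of comparisons between the comparator and intervention cohorts, with continuous outcomes analysed using t-tests" and "categorical outcomes using χ^2^ tests". For the primary outcome this means the chi-squared test, with no covariates.
- **Time trends.** "To account for and disentangle any possible underlying time trends from the effects of AI introduction, regression models will be used to compare outcomes". The models contain "a linear trend in the pre-implementation phase, a step change at the point of AI implementation, and a modification to the linear trend following this". No condition is attached to these models.
- **Case mix.** "If feasible, regression models will be adjusted for known predictors of outcome from both Geneva and sPESI scoring systems". This covers the regressions only, and no criterion for feasibility is given.
- **Threshold.** "Statistical significance will be set according to p value <0.05".

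The section does not say what is concluded if the chi-squared test and the segmented regression disagree, or which of the step and the slope change represents the AI effect.

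**The concern.** In a before/after comparison, anything else that changed between the two periods is mixed with the intervention. That includes the severity of patients scanned, the balance of inpatients and outpatients, and a general improvement in adherence to guidelines. An unadjusted two-sample test attributes all of it to AI.

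The protocol recognises the time-trend part of this problem and plans a model for it, yet gives the primary label to the one analysis that cannot address it. The case-mix part is left to an undefined condition, although the Participant data section already lists the sPESI and Geneva scores, inpatient or outpatient location, and dates for every participant. At stake is whether a significant primary result can be read as an effect of AI at all.

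**Working it through.** The document gives no power calculation or expected concordance, so there is no stated figure to reproduce. The calculations below show the size of the problem under stated assumptions.

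**Inputs from the protocol.** About 3500 scans over 24 months and PE prevalence of 12% to 15% (Sample size). Two 12-month cohorts separated by a 1-month implementation phase (Study population and setting).

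**Assumptions.** Equal cohorts, analysis restricted to PE cases, baseline concordance 60%, uniform accrual, two-sided 5% test, and no AI effect.

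**Cohort size.** 3500 / 2 = 1750 scans per cohort. 1750 × 0.12 = 210 and 1750 × 0.15 = 262.5, so 210 to 262 PE cases per cohort.

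**Drift.** The cohort midpoints are at months 6 and 19, which are 13 months apart. A drift of d points per month produces a difference of 13d in the unadjusted contrast. The chance of significance is approximately Φ((13d − 1.96·SE₀)/SE₁), plus a small opposite tail. SE₀ is the pooled and SE₁ the unpooled standard error.

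Worked case: d = 0.5 points, n = 210. The difference is 6.5 points (60% against 66.5%), SE₀ = √(2 × 0.6325 × 0.3675 / 210) = 0.0471 and SE₁ = 0.0469. Then (0.065 − 0.0922)/0.0469 = −0.58, and Φ(−0.58) = 0.28.

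| Drift per month | Spurious difference | Significant, n = 210 | Significant, n = 262 |
|---|---|---|---|
| 0 | 0 | 5% | 5% |
| 0.25 points | 3.25 points | 10.5% | 11.9% |
| 0.5 points | 6.5 points | 28% | 34% |
| 1 point | 13 points | 81% | 89% |

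If all 1750 scans per cohort formed the denominator, the figures would be 51% at 0.25 and 98% at 0.5 points per month.

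**Case mix.** The bias is the shift in prevalence of a risk group multiplied by the difference in concordance between risk groups. A 10-point shift with a 20-point difference gives 0.10 × 0.20 = 2 points and a false-positive rate of 7.0% to 7.6%. A 20-point shift with a 30-point difference gives 6 points and 24.6% to 29.5%.

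**Which models remove drift.** In simulation with no AI effect, the segmented step term was significant in about 5% to 6% of runs at each drift tried (0, 0.5 and 1 point per month). Adjusting for cohort and month of year does not help. Each cohort covers a full year, so month is already balanced and the 13-month gap is untouched. False-positive rates stayed at 26% to 32% (0.5 points) and 82% to 89% (1 point).

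**Price of the step term.** Fit a line in each cohort and compare the two at month 13. Accrual time in each cohort has variance 12²/12 = 12. The pre-implementation line is extrapolated 7 months from its mean: 1 + 49/12 = 5.08. The post-implementation line is taken back 6 months: 1 + 36/12 = 4. The variance ratio to the simple contrast is (5.08 + 4)/2 = 4.54, so the standard error ratio is √4.54 = 2.13.

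At 60% concordance the simple standard error is √(2 × 0.6 × 0.4 / n) = 0.0478 (n = 210) or 0.0428 (n = 262). The 95% half-width is then 9.4 or 8.4 points for the simple contrast and 20.0 or 17.9 points for the step.

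**The case against.** The strongest reply has four parts.

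First, the deciding test is named. A reader might infer that no rule says which of chi-squared, step or slope change decides, so that success could be claimed from any of them and the error rate inflated. The text does not support this. It calls the unadjusted comparisons primary, so on its face the chi-squared test decides at 5%. What remains open is what the regression does to the conclusion, and through which term.

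Second, a reader might infer that all adjustment is conditional. It is not. The segmented regression for time trends is planned without condition, and only the Geneva and sPESI covariates depend on feasibility.

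Third, some caution about feasibility is reasonable. If concordance is high, a model with eleven month terms and separate sPESI items could be overloaded. Covariates come from clinical records, including paper notes, and analysis is complete-case. This argues for a small model, not for leaving adjustment optional.

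Fourth, Table 1 calls the study exploratory and a feasibility study, the Sample size section disclaims formal power, and covariate lists or rules for disagreement often sit in a full protocol or SAP that is not shown. That excuses missing detail. It does not excuse the choice of primary analysis, which this article makes explicitly and an SAP would inherit.

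**Conclusion.** The point stands in this form: the article fixes an unadjusted chi-squared test as the primary analysis of a non-randomised before/after study, while stating that regression is needed to separate time trends from the AI effect. Adjustment for patient risk is confined to the regressions and is optional, and the bearing of the segmented estimate on the conclusion is not fixed.

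Followed as written, the headline contrast carries any secular drift and any case-mix difference. At 0.5 points of drift per month the nominal 5% error becomes 28% to 34%. The 60% baseline, the drift values, the equal split and the PE-only denominator are assumptions. The protocol treats drift as possible but gives no figure for it, and does not restrict the primary outcome to PE-positive patients. The direction of the conclusion does not depend on these values, but its size does.

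A reader might also infer that adjustment would make the comparison free of confounding. It would not: the collected data can remove measured case-mix differences only, and no case-mix model removes drift.

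**What to change.** Reword the statistical analysis section as follows.

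1. **Primary analysis.** Patient-level regression of guideline concordance on cohort, adjusted for a small prespecified set such as total sPESI score and inpatient or outpatient setting, reported as a standardised risk difference with a 95% confidence interval. Remove the feasibility condition for this model. With sPESI as a single linear term there are three parameters besides the intercept. Even at an assumed 90% concordance, 420 to 525 PE cases give 42 to 52 non-concordant patients, about 14 to 17 per parameter.
2. **Unadjusted t-tests and chi-squared tests.** Label them descriptive.
3. **Segmented regression.** Keep it unconditional, as a named key analysis reported beside the headline, with the step change as its decisive term.
4. **Attribution rule.** State that a difference is attributed to AI only if the step estimate is compatible with it in direction and size. Because the step is imprecise, compatibility should be judged on the estimate and its interval, not on whether the step reaches p<0.05.

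No new data are needed, and the change should be made before unadjusted results are seen. The downsides are a slightly more complex headline analysis, the loss of some patients with missing covariates under complete-case analysis, and a step estimate with about 2.1 times the standard error of the simple contrast, which may leave the attribution to AI unresolved.
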